### Standard psychological treatment

Standard psychological treatment in the Clinic for Traumatized Refugees is inspired from a broad range of theoretical models such as narrative therapy, cognitive therapy, social psychology and neuro-affective therapy. EMDR is part of the treatment options in the clinic, but is *not* offered to participants in the trial.

A therapy course with verbal therapy is based on a phased treatment of traumatic experiences. The therapy course is adapted to the individual needs of the patient and their symptom load. The overall goals are alleviation of symptoms and normalization; and aiding the patient to understand that symptoms are normal reactions to abnormal incidents. Another goal is to promote patients’ reflection, making way for new insights and decrease conditional reflexes. Phase 1 is focused on general stabilization and basic resourcing and the buildup of trust, making way for the formation of a therapeutic alliance. The work is directed to strengthening the daily level of functioning, to learn techniques to regulate affects, increase affect tolerance, and to create a common understanding of symptoms and discomforts. In phase 2 a processing of traumatic memory is taking place, enabling the patient to break with avoidance behavior, and begin integrating the traumatic memories in the life narrative. Phase 3 includes personal integration and rehabilitation. The phases are not necessarily carried out in a sequence, where one phase comes to an end before the next begins, but rather the phases tend to overlap each other throughout the course of therapy.

If a patient wishes to stop treatment, the clinical team find another suitable treatment modality.

### Assessment of treatment fidelity

Both music therapists and psychologists receive clinical supervision from experienced supervisors. All clinicians report on each session in a special field in the data collection system directly after the session. In this way treatment fidelity can be monitored throughout the study, and violations can be reported. Additionally, the music therapists complete notes of music pieces and inductions accompanying the music listening, and the absence of music listening in a treatment can be noticed.

## Outcome measures

The primary outcome measure is the therapist-administered Harvard Trauma Questionnaire (HTQ) [71], demonstrating an acceptable reliability in different languages, including Arabic [72, 73]. The first 16 items of part IV are used, describing to which degree the participants felt disturbed by trauma symptoms corresponding with the PTSD diagnosis in DSM-IV. The scale has three subscales: avoidance, hypervigilance and intrusion.

Eight of the HTQ questions are included in the scale PTSD-8 [74], which is administered at the beginning of sessions 5 and 10 (of 16 sessions) to monitor the effect on trauma symptoms during treatment.

### Secondary outcomes

The secondary outcomes assess changes in attachment and dissociation, both factors have been associated with PTSD and Complex PTSD, playing a role for the therapeutic alliance, relational capacities and ongoing development of integrative capacity in the patient. The Revised Adult Attachment Scale (RAAS) [75] is a revision of the original Adult Attachment Scale evaluating the experience of emotional closeness or distance with 18 questions which are answered on a Likert scale with 5 points ranging from “right for me” to “not at all right for me.” The questionnaire indicates whether a person has a predominantly safe, defensive/anxious or dependent attachment style. Safe attachment measured with RAAS correlates negatively with the PTSD diagnosis [76].

Two dissociation scales are included in the study. The Dissociative Symptoms Scale (DSS) [77] evaluates moderate to severe levels of depersonalization, de-realization, gaps in awareness or memory, and dissociative re-experiencing. The DSS is applied with the permission from the developers. The 20 questions are answered in relation to the amount of time that the person experiences each symptom on a 5-point Likert scale ranging from “not at all,” “once or twice a day” to “more than once a day.” The scale shows good psychometric properties [77].

The Somatoform Dissociation Questionnaire (SDQ-20) [78, 79] is a supplementary scale for the evaluation of somatic dissociation, but going a little more in depth. The 20 questions ask about dissociative symptoms that are evaluated on a 5-point Likert scale, ranging from “does not at all fit with me” to “fits extremely well with me.” If an item is acknowledged as fitting for the person, there is an additional question to whether a physician has provided a physical diagnosis that explains the symptom or not. The scale has good psychometric properties and has been found to correlate with self-reported traumatization [78, 80].

The WHO Well-being-5 (WHO-5) is a short form that allows information of general health and absence of distress to appear [81]. The scale consists of five questions measuring quality of life and well-being (joy, energy, healthy rest, motivation and meaningful activities).

At the end of each session a session evaluation is carried out. Music therapy patients are asked to what degree they have used the music method since their last session. All patients are asked to rate to what extent they feel understood and heard by the therapist (0–10) and how helpful they find the session (0–10) to be. They are also asked to name the most important themes of the session, and what they think they will remember/tell their spouse when returning home. The music therapists are collecting data about the use of music, intervention and themes of the session.

### Translation of scales

All scales are available in Danish, English and Arabic. The author SM performed a translation of SDQ-20, DSS-20 and RAAS into Arabic together with an expert group of experienced Arabic-Danish translators, and the author BB performed a translation of SDQ-20 from Swedish to Danish with the help of a Swedish health-informed translator living in Denmark. The translations were back-translated and checked for misspellings and misinterpretations following the guidelines for translation of research questionnaires (Process of translation and adaptation of instruments, WHO, n.d.).

### Explorative outcome measure: assessment of levels of neuropeptides

As mentioned in the background section several studies have assessed oxytocin in connection with PTSD patients, but only after a single intervention. In the present study, we chose to assess the change in in neuropeptide concentrations following a single intervention and the possible changes in basic levels of the neuropeptides oxytocin, beta-endorphin and substance P after treatment. This remains an exploratory part of the trial.

The collection of saliva is ethically less invasive than blood sample collection, it is self-administered and it takes less than a minute to collect a sample.

### Collection and analysis of saliva samples

The collection of saliva samples is carried out by the therapists in the project. A description of the collection procedure is available for all therapists. 1–2 ml of saliva are collected from the patients in a tube (Disposable plastic tube, Thermo Scientific Nunc 345,608, 14 ml) or a small petri bowl (Thermo Scientific Nunc IVF ICSI Dish). The patients are given the possibility to be alone in the room while collecting saliva. The therapist fills out a label with patient ID, time and date and data time point. The female patients are asked whether they are menstruating, and this is noted on the label, as it could influence the hormone levels. The samples are stored immediately in a freezer at − 18–20 °C. The samples are transported to the Translational Unit, Neuropsychiatry Unit (TNU), Aarhus University in a flamingo box with cool freeze bricks (Farusa emballage, foam refrigerant bricks) at a temperature of − 70 °C. At TNU they are stored at − 80 °C until further handling. When all samples have been collected, the levels of oxytocin, beta-endorphin and substance P will be analyzed using a Luminex and a Milliplex kit (Human Neuropeptide Magnetic Bead Panel; Neuroscience Multiplex Assay (HNPMAG-35 K)).

#### Procedures

After assessment by the visitation team and at the team conference, eligible patients are invited to participate in the study by one of the three music therapists/researchersThe patient is informed orally and in writing about the studyIf the patient accepts participation, informed consent is signed by patient and therapist. If participation is rejected the patient is offered other treatment in the clinicBaseline measurement is carried out by the music therapists/researchers. Information about health according to height, weight, exercise, use of alcohol, smoking habits, symptoms and medication is collected during the visitation procedures in the clinic, and transferred to the dataset by the researchers. All data collection is carried out on laptops with a data collection environment called Xpsy (see below in the “Data management” section). Demographic data and information relevant for the trauma history are collected and scored regarding age, gender, country of origin, native language, education, civil state, number of children at home, whether the patient has been sexually or physically abused during their childhood, imprisonment (number of weeks), exposure to torture, number of weeks on flight, number of weeks in refugee camps and/or asylum centers. The patient fills out self-report questionnaires and a saliva sample is collected. The scoring of the primary questionnaire HTQ is done by a psychologist or trained music therapist, as it requires specialist knowledge and training, and is based on an interview with the patient. The secondary questionnaires are filled out in the presence of one of the researchers or with the presence of a translator trained in assisting the scoring of the questionnairesThe patient is randomized to treatment with music therapy or standard treatmentTreatment is carried out according to the descriptions under “Interventions”Patient data are recorded in all sessions (session evaluation), session data regarding use of music and themes for the therapy are collected by the music therapists with the help of translatorsData collection (PTSD-8) is carried out in sessions 6 and 11 and saliva samples are collected in sessions 3 and 14 (see “Outcome measures” and the flow chart in Fig. 1)After the last session, a post-treatment data collection session is scheduled, where all questionnaires are filled out, HTQ is scored by an external psychologist (and translator) who is not a part of the treatment team and who is blinded to the patient’s treatment group. Three questions regarding the patient’s own evaluation of their current life situation are posed by the music therapist/researcher. In order to leave out confounders of diurnal variation, the time of the meeting is scheduled so that the collection of saliva can occur at the same hour as the baseline sample was collected. Any need for additional treatment is assessed by the clinical team. If additional psychotherapeutic treatment is needed, the participant is excluded from follow-up measurement. All participants who have completed the protocol are invited to a 6-month follow-up session, where questionnaires and saliva samples are collected, with an external psychologist assisting in scoring HTQ, and a trained translator, who is blinded to the affiliation, assisting in scoring the remaining questionnaires

Adherence to treatment is monitored through the evaluation of sessions, and in case of dropout participants are asked about their reasons for stopping treatment, if possible. A research log including dropout information is kept by the researcher team. Additional sessions in the clinic during participation (such as body therapy or social counseling) and change of medication are followed in the patient journal and scored in the data collection environment.

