### Dose

A significant correlation between dose and response has been found for music therapy treatment with serious mental disorders, with small effect sizes after three to ten sessions and large effects after 16 to 51 sessions [66]. A review of quantitative studies of GIM concluded, that at least ten sessions should be provided for clinical populations [67]. In our pilot study, 16 sessions provided significant changes with large effect sizes on all the outcome measures. This number of sessions also fits with the psychiatric clinic’s standard length of treatment. We chose to repeat the 16 sessions as dose for both treatment arms in the present study.

The patients participate in weekly sessions, lasting 60 min. If any cancellations occur the treatment period is prolonged until all 16 sessions have been received. Should the participant encounter any given events that would lead to further traumatizing by way of circumstances outside therapy, treatment can be prolonged to as many as 20 sessions, after consultation with the treatment team and the physician. Hence, a margin of 25% is accepted (from 12 to 20 sessions). In both music therapy and the comparator treatment a phase-oriented treatment according to Herman [68] is carried out, including a stabilizing phase, a trauma-exposure phase and a reorientation phase (if possible). The development of a safe therapeutic relationship and verbal processing are components in both psychological standard treatment and trauma-focused GIM. Thereby, the professional adaptation of music as a therapeutic medium, including the way that music influences the therapeutic relationship, is the independent variable in the trial.

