#### Statistical methods

Statistical analysis will be carried out in the statistical environment R [82] in cooperation with the statistical department in the research unit of Region Zealand and PFI Region Zealand (Production, Research and Innovation Unit). Data will be treated according to the intention-to-treat principle. Analysis of all data will take place after the conclusion of data collection. Following the initial screening of the data significance tests concerning differences between standard treatment and music therapy will be carried out in order to assess the non-inferiority of music therapy. Significance and variance for the primary outcome measure will be calculated with analysis of covariance (ANCOVA), including data from five measuring points. Secondary questionnaire outcome data will also be calculated with ANCOVA, using three data points. Correlations between trauma symptoms, attachment, dissociation and demographic parameters are investigated. A regression analysis will be applied to look for predictors of improvement of trauma symptoms (HTQ) and change of attachment style, as well as predictors for improvement connected to treatment (music therapy or standard treatment). Analysis of hormones will be split up in an ANCOVA testing variance between groups and with time (baseline to follow-up), and simple significance tests of change after single sessions (between the third and 14th session and between the interventions). Session satisfaction data will be treated with descriptive statistical methods.

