#### Power calculation

In order to estimate the level of power we reviewed randomized and non-randomized trials where refugees suffering from PTSD were treated with stabilization and trauma exposure strategies with cognitive and narrative elements corresponding to the standard treatment in our study, and where the Harvard Trauma Questionnaire was used to measure changes in trauma symptoms (the primary outcome in the current study). The variations in the studies were considerable, and we chose to only look at studies that had a number of sessions that were similar to the current study, and where the mean baseline value of HTQ were around 3.3, a value that we found to correspond to our population in the pilot study [18, 62, 83–86]. Non-significant differences between 0.1 and 0.5 was found in HTQ from pre to post treatment. Based on our clinical experience and data from these studies, we estimate a clinical insignificant difference of 0.3 as the maximal difference between music therapy and standard treatment to confirm the non-inferiority hypothesis. A mean standard deviation of 0.48 on post-scores of HTQ was calculated from the studies referred above.

The power calculation was based on a significance level of 0.05, power 0.08, *d* = 0.3 and *SD* = 0.48. The calculation was carried out with software from Epi-info 7 (http://wwwn.cdc.gov/epiinfo/) in cooperation with Department for Statistics, Psychiatric Research Unit, Region Zealand and PFI.

The result indicates a minimum of 64 participants (32 in each group).

Adherence to music therapy has been found to be good in psychiatric patients with a low dropout rate (11.5%) [87]. In three former randomized clinical studies on psychological treatment of refugees with large samples low dropout rates (7–10%) were demonstrated at follow-up [21, 83, 88].

We have, therefore, chosen to include a dropout rate of 10% and thus end up with *n* = 70 (35 in each group).

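### The post-treatment HTQ is tied to the last therapy session, and no route is described to a comparable score for participants who stop early, which puts the intention-to-treat non-inferiority comparison at risk

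*Protocol article*

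**What the plan says.** All references are to the protocol article.

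- **Timing of the visit (Procedures).** "After the last session, a post-treatment data collection session is scheduled, where all questionnaires are filled out". A blinded external psychologist scores the HTQ at this visit. No time from randomisation is given.
- **Length of a course (Dose).** Sessions are weekly and 16 are planned. "If any cancellations occur the treatment period is prolonged until all 16 sessions have been received". Between 12 and 20 sessions is accepted.
- **Dropouts (Procedures).** "in case of dropout participants are asked about their reasons for stopping treatment, if possible". A research log records dropout information. No outcome visit is mentioned for them.
- **Six-month follow-up (Procedures).** Here a restriction is written out: "All participants who have completed the protocol are invited to a 6-month follow-up session". The sentence on the post-treatment visit carries no such restriction.
- **Analysis (Statistical methods).** "Data will be treated according to the intention-to-treat principle". The primary ANCOVA uses five measuring points, two of them the PTSD-8 short form taken during treatment.
- **Sample size (Power calculation).** The minimum is 64. "We have, therefore, chosen to include a dropout rate of 10% and thus end up with" 70, or 35 per group.
- **Expected direction of dropout (Risk of bias).** Because music therapists run the information meetings, participants may be more inclined to leave standard treatment, which the authors say could favour music therapy.

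**The concern.** An intention-to-treat comparison needs an outcome for people who stop treatment, taken at about the same time as for everyone else. Here the visit is triggered by the end of therapy. A patient who simply stops coming has no planned final session to trigger it, and the procedure given for that patient collects reasons, not an HTQ score.

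This matters more in a non-inferiority trial than in most. If patients who leave a therapy because it does not suit them also leave the dataset, the failures that the trial has to rule out become harder to see. The article gives reasons to expect dropout to relate to treatment. Potential harms lists reactions specific to music, such as sound hypersensitivity and restimulation of trauma, while Risk of bias expects more dropout from standard treatment. A statistical analysis plan can model missing scores but cannot collect them, so visit timing has to be settled in the trial procedures.

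**Working it through.** **1. The plan's own sample size.** Inputs from Power calculation: margin 0.3, SD 0.48, significance level 0.05, power printed as 0.08 and read as 0.80. Assuming a one-sided test and no true difference:

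n per group = 2 × (0.48/0.3)² × (1.645 + 0.842)² = 31.7, so 32 per group and 64 in total. This matches the article. One-sided 0.025 would give 41 per group, or 82, so the stated figure implies one-sided 0.05.

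Ten per cent of 70 is 7 participants, leaving 63, with power of about 0.80. If all 70 were measured, power would be about 0.83. Sample size is therefore not the problem; any harm is bias.

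**2. The two readings of the visit trigger.**

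- *Final session of a course.* Someone who stops early never reaches it, and no visit is triggered.
- *Last session attended.* Someone who stops at session 3 is scored about 3 weeks in. Completers are scored after at least 16 weekly sessions, and the mean course in the pilot was 26 weeks (Pilot study).

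Neither reading gives an early stopper a score comparable with a completer's.

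**3. What the in-treatment data add.** PTSD-8 has eight of the 16 HTQ items. It is taken at sessions 5 and 10 (Outcome measures; Procedures says 6 and 11). A patient who leaves before the first of these contributes only a baseline value.

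**4. Size of the possible bias.** Let pM and pS be the proportions unmeasured in the music and standard arms. Let dM and dS be how much worse (higher HTQ) those patients are than completers in the same arm. The completer difference departs from the all-randomised difference, in favour of music therapy, by

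bias = pM × dM − pS × dS.

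With 32 analysed per arm, SE = 0.48 × √(2/32) = 0.12. With a true all-randomised difference of 0.3 and a one-sided 5% test, the false non-inferiority rate is 1 − Φ(1.645 − bias/0.12).

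| pM | pS | dM | dS | Bias | False non-inferiority rate |
|---|---|---|---|---|---|
| 10% | 10% | equal | equal | 0 | 5% |
| 10% | 10% | 0.3 | 0 | 0.03 | 8.2% |
| 10% | 10% | 0.5 | 0 | 0.05 | 11.0% |
| 11.5% | 7% | 0.5 | 0.5 | 0.0225 | 7.2% |
| 7% | 11.5% | 0.5 | 0.5 | −0.0225 | 3.3% |

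The 7%, 10% and 11.5% rates appear in Power calculation; their assignment to arms is assumed, and all deficits are assumed. A simulation with 35 per arm, 10% dropout and completers only gave 5.1%, 8.3% and 11.2% for dM of 0, 0.3 and 0.5 with dS = 0, in line with the formula. A bias of 0.05 is 0.05/0.3 = 17% of the margin.

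**The case against.** The strongest reply is that much of this rests on silence in a condensed article. A reader might infer that dropouts are excluded from the post-treatment HTQ and that the trial will in fact compare completers. The documents do not say so. The limit to those who completed is written only for six months, and its absence from the post-treatment sentence could mean that this visit is open to all. Accepting 12 to 20 sessions also means that someone who stops at session 12 is within plan. The assessment schedule in Fig. 1 is not available here.

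The 10% allowance should not be over-read either. Inflating for dropout is routine and compatible with intention to treat. Part of the evidence behind it (7–10%) was observed at follow-up in earlier trials, so it cannot all be assigned to the post-treatment visit.

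A reader might also infer that any bias favours music therapy. The 8% and 11% rows need music-arm dropouts to do worse than their completers while comparator dropouts do not, and nothing in the article supports that asymmetry. With more dropout from standard treatment, the direction the article expects, and equal deficits in the two arms, the rate falls below 5%.

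These objections stand against the stronger readings. They do not remove the gap. The article does state the visit trigger and what is done with dropouts, and on either reading of the trigger an early stopper has no comparable blinded score.

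**Conclusion.** The point holds as a risk, not as a demonstrated completer analysis. The article promises intention to treat and ties the main post-treatment outcome to therapy attendance, but describes no route to a comparable HTQ score for those who stop early. On the plan's own allowance, up to about 7 of 70 participants are affected, and fewer if part of that loss arises only by six months.

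The direction of bias is unknown. In the illustrative scenarios the false non-inferiority rate at the margin lies between about 3% and 11%, with no distortion when dropout rates and deficits are equal. Those figures rest on an assumed SE of 0.12, an assumed one-sided 5% level (consistent with the stated 64), complete loss of dropouts' post-treatment scores, and assumed deficits of 0 to 0.5 HTQ points. They also ignore any partial recovery through the PTSD-8 data.

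**What to change.** In Procedures:

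- Schedule the post-treatment HTQ, scored by the blinded external psychologist, for every randomised participant regardless of sessions attended.
- For anyone who stops early, set this visit at a prespecified calendar time from randomisation that matches the expected end of a full course, for example within the 4 to 6 months given in Setting and in Limitations and complexities.
- Invite dropouts to this visit as well as asking for their reasons.

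In Statistical methods, state that these scores are analysed in the allocated arm. In Power calculation, state that the 10% allowance covers missing HTQ scores and not stopped treatment.

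The cost is a short amendment and up to about 7 assessments, among the 70 randomised, to be pursued outside treatment. Some dropouts will decline, and those who attend will be dated by calendar and not by session count. The change concerns the timing of assessment only and leaves clinical care untouched.

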**Methods:**

A randomized controlled study with a non-inferiority design is carried out in three locations of a regional outpatient psychiatric clinic for refugees. Seventy Arabic-, English- or Danish-speaking adult refugees (aged 18–67 years) diagnosed with PTSD are randomized to 16 sessions of either music therapy or verbal therapy (standard treatment). All participants are offered medical treatment, psychoeducation by nurses, physiotherapy or body therapy and social counseling as needed. Outcome measures are performed at baseline, post therapy and at 6 months’ follow-up. A blind assessor measures outcomes post treatment and at follow-up. Questionnaires measuring trauma symptoms (HTQ), quality of life (WHO-5), dissociative symptoms (SDQ-20, DSS-20) and adult attachment (RAAS) are applied, as well as physiological measures (salivary oxytocin, beta-endorphin and substance P) and participant evaluation of each session.

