#### Blinding

There is no blinding connected to the randomization of intervention. Questionnaire data are blinded to all clinicians who are performing the treatment and data collection in the project, so that none of the clinicians or researchers have access to completed questionnaire data from their own patients or any other participant in the trial. This ensures that the clinical processes are not influenced by the outcome results data.

External psychologists are called in to assist the scoring of HTQ post treatment and follow-up, they are blinded to the treatment of the participant. Data remain concealed until the entire trial is completed.

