### Risk of bias

In a psychotherapy trial such as this, it is often not possible to blind the intervention of the participants, and there can be an influence of their knowledge of being in the intervention or the control group. However, in this trial we investigate two types of treatment in a single clinic with equal dose (16 sessions) and equal weight as primary trauma treatment modalities. According to concealment of allocation, the randomization procedure is generated by computer software at Sealed Envelope, and none of the researchers have any influence over the procedure. Baseline tests are carried out before randomization, so that the allocation does not influence the measurement. Psychologists carrying out data collection concerning the primary outcome measure at post and follow-up times are concealed to the allocation (and the patients are not asked about it). Imbalances between treatment groups are prevented by the use of stratification (gender and location).

As music therapists carry out the information meetings and measurement, the participants might be more motivated for music therapy than standard treatment (comparator), and be more likely to drop out from standard treatment. This could possibly influence the results in favor of music therapy. Adherence to the treatment is secured, as none of the participants can cross over to the other group. If a patient drops out from music therapy and is offered standard treatment, they are excluded from follow-up. If participants are offered other types of treatment in the clinic parallel to the assigned treatment, this will be monitored and an analysis of any group differences will be carried out.

Protocol fidelity is assured by data collection of the therapist notes for all sessions, by team supervision and frequent meetings between music therapists and psychologists and in the group of music therapy researchers. The use of Xpsy for data collection ensures that no participant data are analyzed in the wrong group.

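### The abstract promises blind outcome assessment post treatment and at follow-up, but at the post-treatment visit the procedures provide it only for the HTQ

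*Protocol article*

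**What the plan says.** The abstract (Methods) makes a general statement about both later visits: "A blind assessor measures outcomes post treatment and at follow-up".

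The body of the protocol article is narrower:

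- **HTQ, post treatment.** Under Procedures, "HTQ is scored by an external psychologist (and translator) who is not a part of the treatment team and who is blinded" to the treatment group. The Blinding section has the same scope: "External psychologists are called in to assist the scoring of HTQ post treatment and follow-up".
- **Other questionnaires, post treatment.** Procedures says only that "a post-treatment data collection session is scheduled, where all questionnaires are filled out". It names no helper for these scales and states no blinding for them.
- **Life-situation questions, post treatment.** Three questions on the patient's own evaluation "of their current life situation are posed by the music therapist/researcher".
- **Other questionnaires, 6 months.** Procedures names "a trained translator, who is blinded to the affiliation, assisting in scoring the remaining questionnaires".
- **Who measures.** Risk of bias states: "As music therapists carry out the information meetings and measurement, the participants might be more motivated for music therapy than standard treatment". It adds that this might favour music therapy.

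**The concern.** A reader of the abstract will take every outcome at the post-treatment visit to be blind-assessed. The procedures support that for the primary outcome only.

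Research question 2 asks whether Trauma-focused Music and Imagery (TMI) is as effective as standard treatment on dissociation, attachment and well-being, and asks it explicitly from pre to post treatment. The scales behind that question have no stated blinded helper at the visit where it is first answered.

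The one staff member placed at that visit besides the external HTQ team belongs to the experimental arm's profession and knows the allocation. Answers on well-being, attachment or current life can depend on who is in the room. For a TMI patient that person shares the profession of the patient's own therapist; for a patient in standard treatment, that person comes from the other arm's profession. If this tilts answers toward TMI, then in a non-inferiority framework it makes a conclusion of being as effective easier to reach.

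**Working it through.** The documents give no figure on this point, so the check compares the sections.

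**Step 1. Who handles what, by visit (Procedures, unless noted).**

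| Visit | HTQ | WHO-5, DSS, SDQ-20, RAAS | Life-situation questions |
|---|---|---|---|
| Baseline, before randomization | psychologist or trained music therapist | researcher or translator present | not mentioned |
| Post treatment | external psychologist, blinded | completed; helper and blinding not stated | music therapist/researcher |
| 6 months | external psychologist, blinded (Blinding section) | translator, blinded | not mentioned |

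The baseline entry for the secondary scales rests on this sentence: "The secondary questionnaires are filled out in the presence of one of the researchers or with the presence of a translator". It does no harm there, because nobody yet knows the allocation.

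**Step 2. Does the music therapist/researcher know the allocation after baseline?** Yes. Under Randomization, that person enters the patient's data on the website, sees the assigned group at once and also receives it by email. There is one such researcher per location.

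**Step 3. Are treating and measuring roles separate?** Not clearly. The Blinding section speaks of clinicians who both treat and collect data, and of clinicians or researchers having patients of their own. Risk of bias says music therapists carry out measurement. No section excludes them from the post-treatment secondary scales.

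**Step 4. Compare with the abstract.** At 6 months the blinding claim is supported for the HTQ and for the other questionnaires. Post treatment it is supported for the HTQ and for nothing else. The abstract's sentence is therefore wider than the procedures by four questionnaires at one visit.

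**Step 5. Size.** The planned sample is 70, so up to 70 post-treatment visits are concerned. No passage gives the effect of an unblinded helper on any scale. The difference of 0.3 and the SD of 0.48 in the Power calculation section belong to the HTQ and cannot be carried over to the secondary scales. Neither the sample size nor the primary analysis depends on this point.

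**The case against.** The strongest reply is that this is a wording mismatch in an abstract. Much of that reply stands.

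- **The three life-situation questions are not a listed outcome.** They appear under neither the primary, secondary nor exploratory measures. A reader might infer from that sentence that researchers administer WHO-5, DSS, SDQ-20 and RAAS post treatment. No sentence says so. The article is silent on who helps, and such detail may stand in the full protocol. The point rests on the abstract's unrestricted claim against the stated scope of blinding, not on the silence alone.
- **Measurement in Risk of bias is not tied to a visit.** It may refer mainly to baseline, which Procedures assigns to the music therapists. The mechanism given there is motivation and dropout from standard treatment, not answering in front of an unblinded person. The disclosure is real, but it neither covers this route nor sets a safeguard against it.
- **The scales are self-report.** Participants and/or translators type the answers into Xpsy (Data management), clinicians and researchers cannot see completed questionnaires (Blinding), and patients know their own treatment. A blinded helper cannot remove that last source of bias. It can remove only the part due to who is present.
- **The HTQ rater.** A reader might infer that a researcher at the same visit could reveal the allocation to the rater. The documents do not support this. The rater is external and blinded, patients are not asked about their allocation (Risk of bias), and no section puts the researcher in the HTQ interview.

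What remains is that the plan claims a property for all outcomes that its procedures deliver, at the post-treatment visit, for one.

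**Conclusion.** The concern holds in a limited form. The abstract's claim of blind assessment is not matched by the procedures for the secondary questionnaires post treatment, and staff who know the allocation take part in that visit. Pre-to-post results on dissociation, attachment and well-being could be tilted toward TMI. That is a possibility, not a demonstrated bias: it assumes that an unblinded music therapist/researcher is in fact present when the scales are completed and that this presence alters answers. Its size is unknown.

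Two stronger conclusions should not be drawn. The documents do not show that the secondary outcomes are biased, and they give no ground for doubting the HTQ rater's blinding or the primary non-inferiority comparison.

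The matter is worth correcting because research question 2 rests on these scales and the correction is cheap.

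**What to change.** **For visits still to come.** At the post-treatment visit, have the blinded external psychologist, or a blinded translator where one is used, assist with WHO-5, DSS, SDQ-20 and RAAS and pose the three life-situation questions. This extends what Procedures already states for the remaining questionnaires at 6 months. Three details matter:

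- Translators are used only as needed, and Danish and English speakers are eligible, so the external psychologist must cover patients without a translator.
- A translator who interpreted that patient's therapy sessions cannot count as blinded.
- Score the HTQ first, so that nothing said in the other parts can reach that rating.

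The documents do not show the 6-month visit to be free of therapists, because project therapists collect the saliva samples. The change therefore concerns the questionnaires and questions, not sample collection.

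**For visits already held otherwise.** Recruitment began in May 2016, so some may be. Limit the abstract's blind-assessor statement to the HTQ, state who assisted with the post-treatment secondary scales, and report those outcomes as not blind-assessed.

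**Cost.** Revised wording in the abstract and Procedures, approved as a protocol amendment where required, and a little more time from the external psychologist and translator whom Procedures already names for that visit. The sample size does not change.
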